### Evaluating impact of PQIP (RQ9)

We will compare risk-adjusted patient outcomes which are available from administrative data (e.g. mortality, length of stay, readmission to hospital, ‘days alive and out of hospital’ at 30 and 90 days and one year after surgery (Moonesinghe et al. 2019)) in hospitals and patients who are enrolled in PQIP and those who are not. Temporal trends will be analysed using a difference in differences approach. In order to avoid bias associated with different hospital types which may affect patient outcomes irrespective of involvement with PQIP, we will apply coarsened exact matching (Iacus et al. 2012; Bonfrer et al. 2018), matching PQIP and non-PQIP hospitals using pooled data from organisational surveys conducted by the Health Services Research Centre for PQIP and other studies (e.g. SNAP2-EPICCS (Moonesinghe et al. 2017)and the National Emergency Laparotomy Audit (National 2014)) as well as open-access external sources such as NHS England and Department of Health datasets.

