### Limitations

The requirement for patient consent means that the sample may be biased. While this is of less importance for process measures which will be used to evaluate care quality, it is relevant when considering outcomes. We will mitigate this risk through comparison of the PQIP population to the total sample of patients undergoing PQIP included procedures using Hospital Episode Statistics (HES) data. This will enable us to undertake sensitivity analyses which will demonstrate what (if any) biases there are in our sampling.Similarly, our ambition to enable as many hospitals as possible to participate irrespective of local resourcing, means that some hospitals will attempt to recruit all patients who are potentially eligible, and some only a sample. We will again try to mitigate this risk through encouraging hospitals to recruit a random sample of patients and will compare the PQIP sample against the HES-defined population at local level as well.

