### Research questions

What is the level of compliance with evidence-based structures and processes for patients undergoing major surgery?What are the rates of complications, failure to rescue (FTR), short- and long- term mortality in patients undergoing major planned surgery in NHS hospitals?How do the rates of adverse outcomes vary over time and between institutions?Are there structural or process related predictors of these adverse outcomes?What is the relationship between different measures of postoperative outcomes (e.g. different measures of morbidity; short and longer-term outcomes, health-related quality of life and disability)?What is the validity and predictive performance of previously published risk prediction models for different perioperative outcomes in the PQIP population?Can existing risk models be improved, or more parsimonious versions developed to support temporally responsive risk adjustment and clinically useful risk evaluation?How representative is the sample of patients recruited to PQIP of the total cohort of patients undergoing potentially eligible procedures in PQIP hospitals?Is there an outcome benefit to hospital and/or patient involvement in PQIP which can be differentiated from secular variation?Can quality of care be improved through a theoretically underpinned complex intervention supporting the use of data for improvement at local level, and do patient outcomes also improve?

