### Evaluating sample validity (RQ8)

One of the objectives of PQIP is to measure and report processes and outcomes from surgery for the purposes of quality improvement. While it is widely accepted that data from a non-random sample of patients within an institution may provide important information about reliability of processes and systems (Peden and Moonesinghe 2016), sampling of patient outcomes should be statistically and conceptually robust so as not to provide biased estimates. Clinical trials and cohort studies which have specific inclusion and exclusion criteria, or which require patient consent, can be criticised as non-representative (and therefore the findings are of limited generalisability) (Deaton and Cartwright 2018). A potential solution to this is to use administrative data to evaluate outcomes; however, in the UK, such data are limited to mortality, hospital readmission and length of stay.

We will address these issues through an evaluation of our sampling strategy using administrative data from Hospital Episode Statistics (HES). For included procedures, an anonymised extract of HES data will be requested from NHS Digital for each hospital. This will enable us to conduct sensitivity analyses comparing patient characteristics (for example age, comorbidity, socioeconomic status using the Index of Multiple Deprivation) and outcomes (mortality, hospital readmission, length of hospital stay) between patients included in PQIP and those who are not. We will do this at individual hospital level and at aggregate (national) level.

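### RQ9 reads the enrolled versus non-enrolled patient comparison as possible PQIP benefit, although RQ8 uses much the same comparison to detect sampling bias and no stated safeguard separates the two at patient level

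*Protocol article*

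**What the plan says.** The RQ9 question in Research questions is: "Is there an outcome benefit to hospital and/or patient involvement in PQIP which can be differentiated from secular variation". The section Evaluating impact of PQIP (RQ9) answers it in three steps:

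- **Comparison.** "We will compare risk-adjusted patient outcomes which are available from administrative data", with mortality, length of stay, readmission and days alive and out of hospital as examples, "in hospitals and patients who are enrolled in PQIP and those who are not".
- **Time.** "Temporal trends will be analysed using a difference in differences approach".
- **Bias control.** Coarsened exact matching, "matching PQIP and non-PQIP hospitals using pooled data from organisational surveys". Its stated purpose is: "In order to avoid bias associated with different hospital types which may affect patient outcomes irrespective of involvement with PQIP".

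The section Evaluating sample validity (RQ8) compares patient characteristics and three outcomes (mortality, readmission, length of stay) "between patients included in PQIP and those who are not", at hospital and national level, as a check on the sampling. The Limitations section gives the reason: "The requirement for patient consent means that the sample may be biased". It adds that this matters when outcomes are considered, and that the comparison with Hospital Episode Statistics (HES) is meant to show what biases, if any, the sampling has. The Discussion reports that random sampling proved largely infeasible and that most sites now recruit by convenience.

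**The concern.** The patient-level part of RQ9 is an effect question in its own right, because the research question names patient involvement alongside hospital involvement. The enrolled group is the same in RQ8 and RQ9, the non-enrolled groups overlap, and the three RQ8 outcomes are all among those named in RQ9. Under RQ8 a difference points to selection; under RQ9 it may count as benefit. The article gives no rule for dividing a difference between the two.

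At stake is a published claim that patients who take part do better (or worse). Part or all of such a difference could come from who was approached and who consented. The authors recognise this threat in Limitations and in the Discussion, but the RQ9 section does not carry it over.

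**Working it through.** **Step 1. Does any stated safeguard reach the patient-level comparison?**

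- *Matching.* It pairs hospitals on organisational features. It does nothing about who consents within a hospital.
- *Difference in differences.* The method works on repeated cross-sections of different patients, so it does not matter that each patient has one index operation. It does need the enrolled group to have a counterpart in the earlier period. Under Participants, enrolment happens at preoperative consent, so before a hospital joins PQIP its would-be consenters cannot be picked out. This is an inference from Participants and the RQ9 section; the article does not state it. Comparing early with late PQIP periods would need stable selection, and the move to convenience sampling makes that doubtful.
- *Risk adjustment.* It helps for factors recorded in both groups. The candidate variables under Dataset include physiology, laboratory results and control of long-term conditions, collected for consenting patients. For non-enrolled patients, the RQ8 section names age, comorbidity and deprivation as examples from HES. Selection on anything outside the administrative record remains.
- *Comparator.* Non-enrolled patients inside PQIP hospitals are treated by teams that receive the feedback, dashboards and events described under PQIP process evaluation, so they are not unexposed. Non-enrolled patients elsewhere also differ by hospital.

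**Step 2. How easily could residual selection look like an effect?** The article gives no figure to reproduce: the target of 70,000 comes without an effect size, power or significance level. The following is illustration only.

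Inputs: n = 70,000 per group (the target from Sample size; an equal comparator is assumed); mortality p = 0.6%, 2% and 4% (the ends of the 30-day range in the Introduction, and an assumed value between them); true PQIP effect zero; residual selection risk ratio RR (assumed); two-sided 5% level (assumed); no clustering.

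With p1 = RR × p, d = p − p1 and pbar = (p + p1)/2:

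- SE0 = √[2 × pbar × (1 − pbar)/n]
- SE1 = √[p1(1 − p1)/n + p(1 − p)/n]
- P(declare benefit) = Φ[(d − 1.96 × SE0)/SE1]

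For p = 2% and RR = 0.90: p1 = 1.8%, d = 0.00200, and SE0 and SE1 are both about 0.00073. So (0.00200 − 1.96 × 0.00073)/0.00073 ≈ 0.78, and Φ(0.78) ≈ 0.78.

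| Assumed RR | p = 0.6% | p = 2% | p = 4% |
|---|---|---|---|
| 0.95 | 0.11 | 0.27 | 0.49 |
| 0.90 | 0.32 | 0.78 | 0.975 |
| 0.80 | 0.865 | about 1.0 | about 1.0 |

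Without selection the rate in this direction would be 0.025. With 35,000 per group and RR 0.90 the probabilities are 0.18, 0.49 and 0.79.

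**Step 3. Does the hospital-level arm share the problem?** Suppose no effect, overall hospital mortality 2% in both periods, and a share s of eligible patients enrolled. Then non-enrolled mortality is pn = 0.02/(s × RR + 1 − s) and enrolled mortality is pe = RR × pn.

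For s = 0.25 and RR = 0.90: pn = 0.02/0.975 = 20.51 per 1,000 and pe = 18.46 per 1,000.

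- Enrolled versus non-enrolled: 18.46 − 20.51 = −2.05 per 1,000.
- Hospital change, all eligible patients: 0.25 × 18.46 + 0.75 × 20.51 − 20.00 = 0.0 per 1,000.
- Hospital change if only enrolled patients form the later period: 18.46 − 20.00 = −1.54 per 1,000.

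Over s = 10% to 50% and RR = 0.80 to 0.90 (both assumed), the patient contrast runs from −2.0 to −4.4 per 1,000 and the enrolled-only version from −1.1 to −3.7. The all-patient hospital version stays at zero.

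**The case against.** The best defence is that the two analyses are not the same estimate. RQ8 is a sensitivity analysis with no risk adjustment stated. RQ9 is risk-adjusted, looks at trends, and asks about effects beyond secular change. Both can be run on the same patients, and RQ8 can serve as a diagnostic for reading RQ9. This stands in part: there is no logical contradiction in reporting both. It does not give the patient-level effect an identifying comparison, and the RQ9 section does not say that RQ8 will qualify it.

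Period definitions and the assignment of methods to each arm may well be in a fuller document, so their absence is not held against the article. The point rests on the patient-level effect question and the contrast that the article does state.

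A reader might go further in four ways that the text does not support:

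- *That selection will be reported as benefit.* Outcomes are risk-adjusted, so only residual selection matters, and the article says only that bias is possible.
- *That all of RQ9 fails.* The hospital arm is matched and can have a before period.
- *That spillover hides any hospital-wide effect.* It blurs only comparisons with non-enrolled patients inside PQIP hospitals; PQIP versus non-PQIP hospitals can still show such an effect.
- *That a small selection effect is certain to reach significance.* An observed ratio at the critical value is not a true ratio: a true RR of 0.95 at 2% mortality is declared a benefit with probability 0.27 in the setting above.

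**Conclusion.** The point holds for the patient-level arm of RQ9 and for nothing wider. As written, residual consent or convenience selection could be reported as a benefit or harm of patient involvement, and no stated safeguard would separate it from a true effect. The conclusion rests on the structure of the comparison, not on a number. The probabilities and the differences per 1,000 depend on assumed selection ratios, group sizes and enrolled shares, and they ignore clustering across more than 126 hospitals; the standard errors are probably too small for that reason.

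This concerns one arm of one of ten research questions. The primary outcome is untouched, and so is the hospital-level arm if it uses all eligible patients. It is worth correcting because the correction is cheap, but it is not a flaw that puts the study in question.

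**What to change.** In Evaluating impact of PQIP (RQ9):

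- State that the effect of PQIP is estimated from the matched hospital-level difference in differences, using all eligible patients in the administrative data whether or not they consented.
- Move the enrolled versus non-enrolled patient comparison to RQ8. Alternatively, keep it in RQ9, labelled descriptive, cross-referenced to RQ8 and not offered as evidence of PQIP benefit.

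In Research questions, amend the mention of patient involvement in RQ9 to match.

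The cost is a change of wording. No data are needed beyond the administrative outcomes already planned for both groups of hospitals. The study gives up an inferential claim about individual patient participation, which the stated design cannot support.

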## Embedded further research

### PQIP process evaluation (RQ10)

One of the core aims of PQIP is to enhance the use of data for improvement by clinical teams, and in so doing, improve processes and outcomes for patients. PQIP may be considered as a complex intervention, which has been developed based on two theoretical frameworks (Normalisation Process Theory and the Theoretical Domains Framework). The intervention involves every part of the measurement, audit and feedback cycle and beyond, and includes collaborative events, regular reporting, dashboards of key measures and the use of social media and educational media to disseminate knowledge and learning. We are evaluating the effectiveness and processes of implementation of PQIP (RQ9) using both qualitative and quantitative methods. Quantitative methods will include the temporal analysis described to address RQs 3 and 9, and longitudinal survey work which will evaluate engagement with the use of PQIP data. The qualitative research includes multi-sited ethnography, using interviews and observations with frontline staff across PQIP and non-PQIP sites and PQIP project team members. The protocol for the qualitative research has been published separately (Wagstaff et al. 2019).

### Nested studies and secondary use of PQIP data

The multi-centre nature of PQIP provides an opportunity to develop and conduct multiple further studies in sub-groups of patients or hospitals, to pilot and evaluate new interventions, and then consider wider implementation. Such interventions may be aimed at improving processes and outcomes of care for patients (core aim 1 of PQIP) or improving the use of data for improvement (core aim 2 of PQIP). Two examples are briefly outlined below.

### pomVLAD

Post-Operative Morbidity reporting using Variable Life Adjusted Displays (pomVLAD), is a nested study funded by the Health Foundation which will develop, implement and evaluate the effectiveness of a near real-time reporting system for risk-adjusted morbidity, mortality and FTR rates. Originally developed to monitor observed versus expected mortality in cardiac surgery, VLAD provides a graphical display of risk-adjusted outcome data over time (Pagel et al. 2013). We plan to develop a recommendation bundle which will be paired with the VLAD display. The enhanced recovery bundle and VLAD dashboard will be trialled in ten early adopter hospitals and evaluated using a difference-in-differences analysis to evaluate its effectiveness and feasibility (Etzioni et al. 2015). If this pilot work achieves its feasibility aims, then there will be potential for wider roll-out of pomVLAD to support quality improvement activity at local level.

### ERAS plus

The ERASPlus initiative (erasplus.co.uk) is an expansion of a quality improvement programme aimed at reducing postoperative pulmonary complications. It was initially implemented, evaluated and found to be clinically effective in a single centre (Moore et al. 2017) and is now being rolled out throughout the Greater Manchester area. The intervention consists of a bundle of care supported by technological innovation (an app for patients to use) including exercise advice and training and targeted interventions to improve pulmonary function and reduce the risk of complications. The expanded ERASPlus initiative is also being funded by the Health Foundation and is working with PQIP to combine data collection efforts to reduce burden on local teams; additionally, this will facilitate comparisons with the non-ERAS + population of PQIP patients.

The PQIP project team will continue to consider requests from external clinicians and researchers collaborate and modify the PQIP dataset to maximise its usefulness for QI or research. After our planned analyses have been completed, a process will be established to enable external clinicians and researchers to apply for access to an anonymised dataset to explore research hypotheses.

## Data management and linkage

All investigators and study site staff comply with the requirements of the Data Protection Act 1998 with regards to the collection, storage, processing and disclosure of personal information and will uphold the Act’s core principles. Patient-level data is entered by local investigators into a secure, electronic, web-based database. This is hosted on servers managed by UK Fast on behalf of the RCoA. Local investigators have access to their own full datasets. An anonymised dataset will be used by the PQIP Project Team for analysis. In this dataset: NHS number is replaced by a unique study patient identifier; date of birth is converted to age on date of surgery; postcode is converted to primary care trust (PCT), strategic health authority (SHA) of residence and the ONS Lower Super Output Area to allow the allocation of the Index of Multiple Deprivation.

The minimum amount of patient identifiable data (including PQIP unique identifier, NHS number, date of birth, gender and postcode) will be extracted from the study database by the PQIP Project Team to allow data linkage to ONS mortality data and Hospital Episode Statistics data from NHS Digital, so that we may track post-discharge outcomes (e.g. hospital readmission) and long-term survival.

## Patient and public involvement

The PQIP patient study addresses areas prioritised by four James Lind Alliance Priority Setting Partnerships (JLA-PSPs): anaesthesia/perioperative care, intensive care, dementia & pressure ulcers. We received detailed structured feedback on our protocol from members of the PCPIE group at the National Institute for Academic Anaesthesia's Health Services Research Centre (NIAA-HSRC). Our project team has two lay members, as does our clinical reference group which provides support and advice on request. Patient representatives are full members of the study team and as such, are invited to comment on all aspects of continuing study development and implementation.

## Impact and dissemination

A report of key findings is produced annually. Quarterly study reports are disseminated to participating sites and published on the study web site. Research resulting from the study will be disseminated by presentations and publications in open-access peer-reviewed journals. Wider dissemination to various stakeholders, including the public, will be achieved via social media, podcasts, short videos, press releases, and written and electronic communications.

## Discussion

PQIP has now been running for 4 years, and was paused for approximately one year during the Covid pandemic, both because elective surgery activity reduced substantially, and because clinical and research teams were diverted to support the emergency response. Review of data collected to that point and discussion with clinical teams has found that the random sampling approach was largely infeasible at hospital level. Therefore, a convenience sampling approach has been adopted by most sites. This further underlines the importance of our planned analyses to evaluate risk of bias in our patient selection and our results.

This also highlighted another challenge with our approach: the direct cost of participation in the study. Hospitals are incentivised to take part because the PQIP patient study is registered on the National Institute for Health Research’s portfolio of approved studies: therefore, sites are financially rewarded for recruiting patients. However, the costs of data collection and entry must be covered locally, and this is a significant challenge, which has limited both site participation and the number of patients recruited per site. Nonetheless, over 126 hospitals have taken part in the PQIP patient study so far, and over 35,000 patients have been recruited.

PQIP has also successfully collaborated with another research team to facilitate an NIHR funded randomised controlled trial to use the PQIP data collection platform and co-recruit into both studies (https://www.journalslibrary.nihr.ac.uk/programmes/hta/NIHR130573/#/) This approach to efficient trial design should bring benefit to patients, clinicians, researchers and provide excellent value for money.

## Conclusion

The PQIP Patient study is the UK’s first national effort to report and improve patient outcomes from major surgery other than mortality and length of stay. A number of research questions will be answered alongside the main purpose of quality improvement in perioperative patient care. The programme is notable in that it is being formally evaluated while in progress.

## Data Availability

Not applicable.
